### Ethical Considerations

This evaluation plan, which is described in more detail below, is approved by the UCSD institutional review board (approval 810254). Data will be collected using unique participant ID numbers that are based on the order of completion and will not be connected to any identifiable information about individual users. The app contains a digital consent form that participants complete before starting study activities. They receive an emailed copy and can access a video walk-through of the consent process. With rolling recruitment, participants can take time to decide and consult with the study team. Focus group members receive individual consent forms after eligibility confirmation. All consent forms are stored on a secure UCSD server accessible only to approved study coordinators. The consent mentions that participants can opt out at any time, and their deidentified data might be used for other studies without their consent. Participants have the opportunity to earn a maximum of US $25 per quarter for completing the surveys. Participants who take part in the focus groups will receive US $60. All incentives will be in the form of digitally delivered Amazon gift cards.

### Process and Participants

A marketing campaign was initiated to advertise the Willo app across the campus during the first quarter of the academic year 2024-2025. The campaign included multiple channels to reach out to students so that they can download and start using the app. Participants who agree to join the research portion of the app launch will provide electronic consent within the app. All participants will be asked to complete web-based assessments through Qualtrics at baseline fall quarter of 2024 and spring quarter of 2025. Additionally, we will conduct 6 focus groups each consisting of 10 students to gather qualitative data about their feedback and experience with the app. If participants consent, they may be contacted up to twice per calendar year until graduation or departure from UCSD.

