### Evaluation Plan

Using the logic model as a foundation, the advisory committee and development team identified key areas that required evaluation. They prioritized metrics that would provide actionable insights for improving the app and its integration into existing campus mental health and wellness services. Drawing on their collective expertise, the committee discussed various data collection methods. They aimed for a mixed methods approach to capture both quantitative and qualitative data, ensuring a comprehensive evaluation. Moreover, recognizing the evolving nature of digital health interventions, the committee built in mechanisms for ongoing review and refinement of both the app and the evaluation process itself.

Throughout this process, the committee emphasized the importance of flexibility and adaptability, acknowledging that the evaluation plan may need to be adjusted as the project progresses and new insights emerge. They also stressed the need for ongoing communication and collaboration among all stakeholders involved in the implementation and evaluation of the student mental health and wellness app. The evaluation questions that could address important outcomes are listed below.

To what extent does the use of the mobile app lead to reductions in symptoms of anxiety, depression, and other common mental health issues among students?How many students download and actively use the app on a regular basis? What user characteristics or engagement patterns are associated with better outcomes?How well is the app integrated with campus counseling, health, and other support services? What are the facilitators and barriers to this integration?What are the key lessons learned from implementing the app, and what modifications or additional support are needed to sustain and scale the program in the long term?

Data collection methods will include pre-post surveys of app users to assess changes in knowledge regarding campus resources, presence and severity of mental health symptoms, emotional self-awareness, stigma and other barriers to care, confidence in and degree of help-seeking behaviors, and overall app usage data (downloads, login frequency, feature engagement). We also plan to conduct interviews and focus groups with app users, campus mental health staff, and other relevant stakeholders.

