### Data Analysis and Interpretation

#### Quantitative Analyses

Quantitative data will be analyzed using appropriate statistical software (SPSS or similar) to determine if users are gaining knowledge about the featured services and resources and if the services and resources that are being highlighted are matching with the desires of the target populations.

To assess changes in mental health and wellness outcomes within and between cohorts over time, we will conduct repeated measures analysis of variance and mixed-effects modeling. These approaches are well-suited for analyzing longitudinal data with repeated observations per participant. The primary dependent variables will include standardized scores from validated instruments measuring mental health and well-being. Independent variables will include cohort membership, time (semester), usage of the Willo app, and engagement with university support services. Interaction terms (eg, time × app usage) will be included to assess potential moderating effects.

A power analysis was conducted using a conservative estimate of small-to-moderate effect sizes, consistent with those commonly reported in similar longitudinal mental health studies. With 850 participants per cohort and repeated measurements across 8 time points, the study is adequately powered (≥80%) to detect meaningful changes in outcomes over time and between groups, assuming an α level of .05.

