## Results

As of March 2025, we are in the process of data collection. Preliminary data that have been collected include >600 responses to surveys from freshman, undergraduate transfer, and medical students. A second round of survey assessments to measure change is expected in April to May 2025. We have also conducted 2 focus groups with undergraduate freshman to date. Two focus groups with undergraduate transfer students and one with medical students are planned for April-May 2025. No data analyses have been performed as of yet. These data will be the baseline for the metrics used, and we plan to repeat the data collection with every cohort biannually.

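### The baseline survey can only follow app download and nothing ties it to first use, so baseline may contain app exposure; a semester time step also ignores the varying follow-up interval

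*Protocol article*

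**What the plan says.** All references are to the protocol article.

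- **Comparison.** Evaluation Plan: "Data collection methods will include pre-post surveys of app users to assess changes in knowledge regarding campus resources". No survey of students before they have the app is described.
- **Route into the study.** Process and Participants says of the marketing campaign: "The campaign included multiple channels to reach out to students so that they can download and start using the app". The next step is: "Participants who agree to join the research portion of the app launch will provide electronic consent within the app".
- **Consent comes first.** Ethical Considerations: "The app contains a digital consent form that participants complete before starting study activities". The same section says: "With rolling recruitment, participants can take time to decide and consult with the study team".
- **Survey timing.** Process and Participants: "All participants will be asked to complete web-based assessments through Qualtrics at baseline fall quarter of 2024 and spring quarter of 2025". Results expects the second round in April to May 2025. After reporting more than 600 responses as of March 2025 and listing the planned second round and focus groups, it adds: "These data will be the baseline for the metrics used, and we plan to repeat the data collection with every cohort biannually".
- **Model.** Quantitative Analyses: "Independent variables will include cohort membership, time (semester"), followed by app usage and engagement with support services. A time by app usage interaction is planned.
- **Logs.** App Usage Analytics says that each user's activity is tracked and organised by session.

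**The concern.** A before-and-after comparison needs a first measurement that precedes exposure, or at least sits at a known distance from it. Here consent is inside the app and the survey comes after consent, so the first measurement cannot precede download. The article sets no limit on the time, or the amount of use, between download and that survey.

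The outcome most open to this is the one the app is built to change. The Objective describes raising awareness of campus resources through preferences set at initial use, and Quantitative Analyses names gain in knowledge of those resources as its first question. If some students browse for days or weeks before the survey, part of any gain is already in their baseline.

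The time by app usage term has two further problems:

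- If usage is counted from download, students who used the app heavily before baseline are classed as high users but show little further change.
- If intervals differ between students, longer intervals allow both more usage and more ordinary change over the year. A step-coded time variable cannot separate the two.

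**Working it through.** **1. The plan's own figure.** Quantitative Analyses states power of at least 80% with 850 per cohort, 8 time points and alpha .05. It gives no numeric effect size, SD or correlation, so the figure cannot be strictly reproduced. It is plausible for simple contrasts (two-sided normal approximation, standardized effect d):

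- Two cohorts of 850 at one time point: SE = √(2/850) = 0.0485. Power is 0.80 at d = 0.136 and 0.985 at d = 0.20.
- Paired change in 850, assumed correlation 0.5: SE = √(2(1 − 0.5)/850) = 0.0343. Power is 0.83 at d = 0.10.

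This point does not dispute the power figure.

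**2. Order of events, from the text.** Consent is within the app, so it follows download. Consent precedes study activities, so the survey follows consent. Hence the survey follows download. Whether it follows *use* is not stated. Recruitment is rolling, and no maximum lag is given.

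**3. Interval between surveys.** The follow-up window, April to May 2025, is in Results. The fall-quarter dates are not in the article; I assume 23 September to 14 December 2024.

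- Longest: 23 September to 31 May = 250 days = 35.7 weeks.
- Shortest: 14 December to 1 April = 108 days = 15.4 weeks.
- Ratio: 250/108 = 2.3.

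If baseline collection ran past the fall, the shortest interval falls further. A baseline on 1 March would leave 31 days, or 4.4 weeks, to 1 April.

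**4. Share of an effect left in the change score.** Illustration only. Let w be weeks of use before baseline, with an assumed 30 weeks from download to follow-up.

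- Linear build-up: share = 1 − w/30.
- Saturating build-up, assumed half-time 4 weeks: f(t) = 1 − 2^(−t/4), share = [f(30) − f(w)]/f(30).

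| w (weeks) | Linear | Saturating |
|---|---|---|
| 0 | 100% | 100% |
| 1 | 97% | 84% |
| 4 | 87% | 50% |
| 8 | 73% | 25% |
| 11 | 63% | 14% |

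**5. What attenuation would do to power.** Take 850 students split 425/425 by app use, a difference in change of d = 0.20 and correlation 0.5. The SD of change is √(2(1 − 0.5)) = 1 and SE = √(2/425) = 0.0686. Power = Φ(0.20k/0.0686 − 1.96), where k is the share remaining.

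- k = 1: 0.83
- k = 0.85: 0.70
- k = 0.70: 0.53
- k = 0.50: 0.31

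The split, d, the correlation and k are all assumed.

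**6. Unit of time.** Surveys are scheduled by quarter (Process and Participants) and survey payments are capped per quarter (Ethical Considerations), but the model's time unit is the semester.

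**The case against.** A reader might infer that baseline already contains app exposure. The text does not establish this. It shows that baseline follows download, not that it follows use. The sentence on downloading and starting to use the app describes the campaign's purpose, not a participant flow. The article does not say where in the app consent appears. Consent and survey at first opening would fit every statement, with almost no prior use.

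A reader might also infer follow-up intervals as short as one month. That conflicts with the fall-quarter baseline in Process and Participants. It rests on taking the responses held in March 2025 as evidence of continued baseline enrolment. The sentence calling the data the baseline can also mean that cohort 1 is the reference for later cohorts. Rolling recruitment concerns time to decide and does not override the named survey quarters.

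Nor can the loss be quantified. An exponential build-up with a time constant of 4 to 8 weeks, for instance, would put 23-39% of a 26-week effect in a baseline taken at 2 weeks and 41-63% at 4 weeks. The shape, the constants and the delays are all assumed, and zero delay is left out.

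Finally, wave coding is an ordinary choice, and a condensed article may leave elapsed-time handling to a fuller document.

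These objections limit the claim but do not remove it. Where consent sits is a design feature that the article fixes. An analysis plan can adjust for exposure before baseline but cannot recover a measurement never taken. The mismatch of semester and quarter is within the article itself.

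**Conclusion.** The point holds in a limited form. The baseline survey necessarily follows download, and nothing shown places it before first use or within a set time of it. Exposure before baseline is therefore possible and uncontrolled, but not proven. If it occurred and the app works, the change in resource awareness would be understated and the time by app usage term distorted.

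The size is unknown from the article and is nil if baseline is completed at first opening. The interval varies about 2.3-fold (15 to 36 weeks) under assumed quarter dates, while the time variable is named only as a semester step and does not match the survey schedule.

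This is a cheap improvement worth making now, not a flaw that invalidates the study. Results states that no analyses have been performed, so the handling can still be prespecified.

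**What to change.** **Cohort 1, in Quantitative Analyses:**

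- Replace the semester time variable with survey wave by quarter plus actual elapsed time between surveys.
- From the app logs, compute days and amount of use before the baseline survey, report their distribution, and adjust for them.
- Count app usage in the model from the baseline date.
- Add a sensitivity analysis limited to students whose baseline fell within a short, prespecified window of first use.

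**Later cohorts:** offer consent and at least the resource-knowledge items during onboarding, before the resource screens are first shown.

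**Cost:** a little more analysis work, a smaller sensitivity set and a slightly longer onboarding. The log-based steps need survey records linked to usage records. The planned usage variable already requires that link, but Ethical Considerations describes IDs assigned by order of completion and unconnected to identifiable information, so the article should say how the link is made.

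**Not proposed, because each is a real trade-off:** dropping the academic calendar from the model, since mood and stress may vary over the year; making the early-baseline subset the main analysis, since it is self-selected; and placing the full battery (Table 2 lists 18 measures) ahead of the resource screens, since that delays access and may cost uptake.

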### Measures

#### Metrics

Metrics to assess the evaluation domains are described below in more detail. We will use several tools and methodologies to collect data, including web-based surveys and in-app data for quantitative and focus groups and interviews for qualitative data. We based much of our approach on that used by the U-Flourish program [1,5] particularly in areas such as the longitudinal assessment of student well-being and the importance of a whole-campus approach to mental health. This collaboration helped us select a suite of evaluation measures that was not only scientifically validated but also of proven use in a large number of college students. This will also enable us to compare some of our findings to others in the U-Flourish network.

#### Surveys and Questionnaires

Validated mental health screening tools (eg, Generalized Anxiety Disorder Scale-7 items, Patient Health Questionnaire-8 items) and health behavior tools (eg, Sleep Condition Indicator-8 items, College Student Subjective Well-being Questionnaire) to measure changes in symptoms over time will be administered (Table 2). We also plan to include custom survey questions to gather user feedback and measure help-seeking behaviors such as their knowledge and interest of student resources and activities.

**Table 2 table2:** List of questionnaires used in the evaluation of the app.

Label	Measure
Resources	Knowledge and Usage of Student Resources
GADS-7	Generalized Anxiety Disorder Scale-7 items
PHQ-8	Patient Health Questionnaire-8 items
WEMWBS-7	Warwick-Edinburgh Mental Wellbeing Scale-7 items
SCI-8	Sleep Condition Indicator-8 items
CSSWQ	College Student Subjective Wellbeing Questionnaire
ULS 4	UCLA Loneliness Scale-4 items
PSS-4	Perceived Stress Scale-4 items
SCOFF	Eating Disorder Diagnostic Scale
GBS	General Belongingness Scale
SCS-SF	Self-Compassion Scale-Short Form
RRS-B	Ruminative Response Scale-Brooding subscale
BCC	Barriers to Care Checklist
BACE-3	Barriers to Care Evaluation
CECA	Childhood Experiences of Care and Abuse
GLTEQ	Godin Leisure-Time Exercise Questionnaire
MSCS	Mindful Self-Care Scale-Mindful Relaxation Subscale
DERS-18	Difficulties in Emotional Regulation Scale

#### App Usage Analytics

At the aggregate level, measures such as weekly and monthly active users, average session duration, and most accessed resources will be tracked to monitor overall app engagement. For each individual user, the app will track their activities such as clicks, pages/resources browsed, events liked, and searched queries. These interactions will also be contextualized by individual app usage sessions. These metrics will help the app learn more about user preferences in general as well as their behaviors with respect to time and further allow the system to define and execute just-in-time adaptive interventions in the future by using varied notifications.

#### Interviews and Focus Groups

We plan to conduct semistructured interviews and focus groups with app users to gather qualitative feedback on their experiences and to understand the barriers, motivations, and perceptions about the app.

### Data Analysis and Interpretation

#### Quantitative Analyses

Quantitative data will be analyzed using appropriate statistical software (SPSS or similar) to determine if users are gaining knowledge about the featured services and resources and if the services and resources that are being highlighted are matching with the desires of the target populations.

To assess changes in mental health and wellness outcomes within and between cohorts over time, we will conduct repeated measures analysis of variance and mixed-effects modeling. These approaches are well-suited for analyzing longitudinal data with repeated observations per participant. The primary dependent variables will include standardized scores from validated instruments measuring mental health and well-being. Independent variables will include cohort membership, time (semester), usage of the Willo app, and engagement with university support services. Interaction terms (eg, time × app usage) will be included to assess potential moderating effects.

A power analysis was conducted using a conservative estimate of small-to-moderate effect sizes, consistent with those commonly reported in similar longitudinal mental health studies. With 850 participants per cohort and repeated measurements across 8 time points, the study is adequately powered (≥80%) to detect meaningful changes in outcomes over time and between groups, assuming an α level of .05.

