For continuous quality improvement, we plan to regularly review the evaluation results with the project team to identify the areas for app refinement and programmatic enhancements and use data to secure continued funding and support for sustaining and scaling the app-based program.

This evaluation plan (Table 1) outlines a mixed methods approach to assess the student mental health and wellness app project on multiple levels—individual student outcomes, community reach and usage, operational feasibility, and long-term sustainability. The plan emphasizes the importance of utilizing evaluation findings to drive ongoing improvement and broader dissemination of effective practices. Rigorous data collection, analysis, and reporting will be critical to demonstrating the value of this initiative to university stakeholders and external partners.

The evaluation team designed a process to evaluate cohorts of the students biannually. This process enables the team to monitor trends and changes at the population level across campus and assess the outreach, effectiveness, and impact of the app. In the first cohort, students who are new to the campus (ie, freshman, transfer, and first-year medical students) will be invited to enroll in the assessments. They will be required to provide informed consent before participating and will be compensated for their time and engagement in the quantitative and qualitative assessments (Multimedia Appendix 3).

**Table 1 table1:** A summary of the evaluation plan for the mental health and wellness app (Willow).

Evaluation domains	Outcomes	Key performance indicators	Data sources and collection method
Campus services awareness, accessibility, and utilization	Improving access to mental health resources, improved efficiency of use of resources for individual psychological counseling, referral to the app by counseling and psychological services & health and wellness providers, improved utilization of on-campus services	Satisfaction, in-app services usage, Counseling and Psychological Services usage, effectiveness and relevance of the app, utilization of campus services	App analytics, in-app rating systems, in-app surveys and questionnaires, focus groups; interviews with counseling and psychological services & health and wellness providers

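### Repeated-measures ANOVA is planned beside the mixed model, but over eight waves it would drop every student who leaves or misses one; the mixed model should be the primary analysis and include student type

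*Protocol article*

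**What the plan says.** Under Quantitative Analyses, the protocol article states that, to assess change within and between cohorts, "we will conduct repeated measures analysis of variance and mixed-effects modeling". It supports both methods with one sentence: "These approaches are well-suited for analyzing longitudinal data with repeated observations per participant". It does not say which of the two carries the conclusion.

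The model terms are given as follows: "Independent variables will include cohort membership, time (semester), usage of the Willo app, and engagement with university support services". Interactions such as time by app usage are to be added. Student type is not in this list.

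The power statement claims that "the study is adequately powered (≥80%) to detect meaningful changes in outcomes over time and between groups". This rests on 850 students in each cohort, eight waves and a significance level of .05.

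Follow-up is described under Process and Participants: "If participants consent, they may be contacted up to twice per calendar year until graduation or departure from UCSD". Only two waves have dates there, fall 2024 and spring 2025. Ethical Considerations adds that participants may opt out whenever they wish. On the make-up of the first cohort, Evaluation Plan says that "students who are new to the campus (ie, freshman, transfer, and first-year medical students) will be invited to enroll".

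**The concern.** The two methods treat incomplete follow-up differently. Standard repeated-measures ANOVA needs one value per student at every wave and deletes a student with any gap. It assumes sphericity when there are more than two waves, and it has no place for a covariate that changes by wave. A likelihood-based mixed model uses whatever waves a student has and accepts usage measured wave by wave.

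The article's own design makes incomplete follow-up certain for some students. At no more than two contacts a year, eight waves take about four years, and contact stops when a student graduates or leaves. An eight-wave ANOVA would therefore describe only students who stayed and answered every time, and it would discard data already collected from the rest. With both methods planned for the same question on different sets of students, they can also give different answers.

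Student type matters for a related reason. The first cohort mixes freshmen, transfers and first-year medical students. If these groups leave at different times or follow different trends, the students behind each wave's average change over time, and the listed terms do not account for that directly.

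**Working it through.** **Inputs from the article.** 850 students per cohort, 8 time points, α = .05 and power of at least 80% (Quantitative Analyses); at most two contacts a year (Process and Participants).

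**Assumptions (not in the article).** Wave-to-wave retention r; the share s of a cohort that leaves before wave 8; effect size (d = 0.2 between cohorts, Cohen's f = 0.10 over time); within-person correlation ρ from 0.3 to 0.7; two-sided testing.

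**1. The article's power figure.** It cannot be reproduced exactly, because no numerical effect size, correlation or test is given. It is plausible if all 850 are analysed. For two cohorts of n each compared at one wave, power ≈ Φ(d√(n/2) − 1.96). With n = 850 and d = 0.2 this is Φ(4.12 − 1.96) = 98.5%. The smallest d with 80% power is about 0.136.

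**2. Duration.** 8 waves ÷ 2 per year = about 4 years.

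**3. Complete cases among students able to stay for all waves.** The share complete is r^7, for seven follow-ups after baseline.

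| r | r^7 | of 850 |
|---|---|---|
| 0.95 | 70% | 594 |
| 0.90 | 48% | 407 |
| 0.80 | 21% | 178 |
| 0.70 | 8% | 70 |

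Half are lost when r^7 = 0.5, that is r = 0.5^(1/7) = 0.906.

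**4. Adding students who leave before wave 8.** Complete cases = 850 × (1 − s) × r^7. For illustration s = 0.33:

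| r | complete cases | power, d = 0.2 between two such cohorts |
|---|---|---|
| 0.95 | 398 | 80% |
| 0.90 | 272 | 65% |
| 0.80 | 119 | 34% |
| 0.70 | 47 | 16% |

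At r = 0.90, if the short-stay third leaves after wave 4 and dropout is permanent, the ANOVA uses 8 × 272 ≈ 2,180 of about 4,210 student-waves observed, or 52%. The mixed model uses all of them.

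**5. Power for change over time in the ANOVA.** Noncentral F with λ = n × 8 × f²/(1 − ρ), 7 and 7(n − 1) degrees of freedom, f = 0.10, sphericity assumed:

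| completers | ρ = 0.3 | ρ = 0.5 | ρ = 0.7 |
|---|---|---|---|
| 407 | >99% | >99% | >99% |
| 178 | 93% | 99% | >99% |
| 119 | 77% | 91% | 99% |
| 70 | 50% | 67% | 90% |

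The within-student comparison therefore keeps good power until few completers remain.

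**6. Student type.** Suppose a third leave after wave 4, differ from the others by 0.3 SD in level, and nobody truly changes. The raw wave mean then moves by 0.33 × 0.3 ≈ 0.10 SD. In a small simulation (20 runs of 850 students), a random-intercept model without student type reduced this to about 0.02 SD.

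**The case against.** The strongest reply is that the remedy is already in the quoted sentence. A mixed model is planned and keeps partial records, so deletion affects only the companion ANOVA. The article does not tie the power statement to the ANOVA, nor does it say that the ANOVA will cover all eight waves. An ANOVA on the two dated waves would not lose students for leaving later, and with two waves sphericity is not at issue; it would keep 850 × r, for example 765 at r = 0.90. All of this is fair and limits the point. It does not remove it: the article names both methods for the same longitudinal question, calls both suitable, and cites eight time points.

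Four stronger readings are tempting, and the documents do not support them.

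- **That the ANOVA loses most students.** Among those able to stay, this needs retention below 0.906 per wave, and no rate is given.
- **That it loses most of the claimed power.** For change over time, 178 completers still give 93% or more at f = 0.10. Between cohorts the loss is larger, but its size rests on assumed retention and departure.
- **That transfer students in particular are all deleted.** This is likely if they stay about two years, but the article gives no programme lengths and no mix of student types.
- **That student type is excluded and its absence biases the time trend.** The list of independent variables is open-ended, so student type is unlisted, not ruled out. A random intercept absorbs most of a difference in level. What remains matters mainly for raw means or where trends differ by type.

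Covariance structure, coding of time and missing-data rules may stand in an analysis plan that is not shown, and their absence is not part of this point.

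**Conclusion.** The point holds in a limited form. The article endorses two analyses of the same question, and one of them fits its own follow-up rules badly. That an eight-wave repeated-measures ANOVA excludes anyone who leaves or misses a wave follows from the method and needs no retention figure. How many students are excluded does need one: from about 30% to 92% of those able to stay, as assumed retention goes from 95% to 70% per wave, and more once early leavers are counted. The mixed model does not suffer this loss. Adding student type is a sensible supporting change and not the correction of a demonstrated bias: the first cohort mixes three types whose follow-up and trends may differ, so cohort membership cannot stand in for it there. The change should be made, but the planned evaluation is not invalid without it.

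**What to change.** In Quantitative Analyses, name one likelihood-based mixed-effects model, using every available wave, as the primary analysis of change, with app usage entered by wave. Delete repeated-measures ANOVA, or keep it only as a sensitivity analysis labelled as complete-case, with the number of students it retains reported. Add student type (freshman, transfer, medical) and student type × time as fixed effects, and report each type's trend over the waves at which that type is observed. The detailed model specification can be left to the analysis plan.

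The cost is a change of wording and a few extra model terms. The mixed model is already planned, and the Results section already describes survey responses by student type. That section also says that no analyses have been performed, so the choice can still be fixed without knowledge of the data.
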